## Abstract

**Purpose:**

For clinical (c) T1N0M0 rectal adenocarcinoma without adverse pathological features, local excision by transanal endoscopic surgery (TEM) is standard; however, contemporary series still report local recurrence (LR) rates of 15–20%. Preoperative unfavorable histopathologic features cannot reliably identify high-risk pT1 disease, and both completion total mesorectal excision (TME) and salvage TME for LR carry relevant morbidity and functional impairment. Building on our prior phase III trial in T2–T3abN0M0 (TAUTEM study), showing that preoperative chemoradiotherapy (CRT) followed by TEM achieved a 7.4% LR with improved postoperative outcomes, we hypothesize that CRT + TEM will increase rectal preservation in cT1N0M0 without compromising oncologic safety or quality of life. The TAUTEM-T1 trial tests this hypothesis.

**Methods:**

Multicenter, prospective, randomized, controlled, phase III superiority trial. Adults with biopsy-proven rectal low or moderate grade adenocarcinoma ≤ 4 cm, located < 10 cm from the anal verge, staged as cT1N0M0, are randomized (1:1) to: CRT (long-course radiotherapy with concurrent capecitabine) followed by TEM at week 10, or TEM alone. The primary endpoint is rectal preservation at 3 years. Secondary endpoints include postoperative morbidity/mortality, CRT-related adverse events, quality of life and anorectal function, and long-term oncologic outcomes (local/distant recurrence, overall and disease-free survival). Planned sample size: 106 patients.

**Results:**

This manuscript describes the rationale and design of the TAUTEM-T1 randomized trial.

**Conclusion:**

TAUTEM-T1 will assess whether preoperative CRT followed by TEM increases rectal preservation in cT1N0M0 rectal cancer without compromising oncologic safety, quality of life, or bowel function.

**Trial registration:**

ClinicalTrials.gov, NCT06450574.

## Introduction

Management of early rectal cancer (stage I: T1–T2, N0, M0) varies widely. For T1N0M0 tumors without adverse pathological factors, local excision (LE) is the standard treatment per international guidelines [1, 2]. However, in T1 lesions with adverse features and in T2 tumors, lymph node involvement may reach 12–28%, warranting total mesorectal excision (TME) [3].

TME, described by Heald, markedly reduced local and systemic recurrence in rectal cancer [4]. However, it is associated with substantial morbidity, including temporary/permanent stomas and relevant mortality, as well as long-term functional sequelae such as genitourinary dysfunction and low anterior resection syndrome (LARS) [5, 6]. In appropriately selected patients, transanal endoscopic local excision (LE) preserves the rectum and is associated with lower morbidity and minimal sphincter/genitourinary impairment [7, 8]. Nonetheless, despite a generally favorable prognosis in stage I disease, standard management does not typically include neoadjuvant therapy [9].

pT1 rectal adenocarcinomas can be classified into two groups according to surgical and histological criteria: (1) favorable prognosis tumors, with a local recurrence risk < 5%; and (2) unfavorable prognosis tumors, with a local recurrence risk up to 29% [10]. Favorable surgical factors include en bloc resection, full-thickness excision, and clear margins > 1 mm. Unfavorable histopathologic factors associated with nodal involvement include depth of submucosal invasion, poor differentiation, venous/lymphatic or perineural invasion, positive margins (< 1 mm), and tumor budding [2, 8]. Depth of submucosal invasion is the main determinant of nodal risk [3], as most other adverse factors occur in < 10% of pT1 cases [1]. Its prognostic value has been questioned by the meta-analysis by Zwager et al. [12], although several included studies had methodological limitations.

There are several classifications used to assess submucosal invasion (Haggitt, Kikuchi, Ueno, Kudo, and Kitajima); however, they present limitations and relevant variability that may influence clinical decision-making. Therefore, our group has proposed the Taulí-pT1 classification, which quantifies tumor invasion according to the area of residual healthy submucosa in the specimen, using a uniform methodology based on a percentage derived from a constant reference point [11]. This classification shows excellent correlation with Kitajima’s and very good correlation with Kudo’s system. Its only requirement for applicability is the presence of the muscularis propria in the specimen. Recently, we have published its validation through interobserver concordance analysis [13].

Recent studies with large cohorts and long-term follow-up (although with retrospective designs) have reopened the debate on local surgery for pT1N0M0 rectal cancer. Leijtens et al. [14] reported, in a series of 150 patients with a median follow-up of 58.9 months, a local recurrence (LR) rate of 22.7% and an overall survival (OS) of 82%; even when stratifying tumors without adverse prognostic features, LR rates exceed 20%. Recently, we have published our long-term follow-up cohort, with a median follow-up of 91 months (IQR: 84), 17 patients (16.3%) developed LR and 14 (13.5%) developed distant recurrence. Five-year rectal cancer–specific and overall survival rates were 95% and 74%, respectively. Among the 88 patients without histopathological or surgical high-risk factors, 13 (14.8%) experienced LR and 9 (10.2%) distant recurrence [15].

An initial proposal of our group when designing this protocol was to apply preoperative CRT followed by TEM in pT1N0M0 rectal tumors with adverse prognostic factors. The main limitation, however, is that these factors can only be identified after the pathological examination of the LE specimen. Preoperative biopsy merely confirms that the lesion is an infiltrating adenocarcinoma, and the only identifiable adverse feature is poor differentiation, present in less than 10% of cases [11, 14]. Therefore, it is not possible to reliably identify high-risk pT1N0M0 patients preoperatively. Moreover, as previously mentioned, in pT1N0M0 tumors without adverse features, LR exceeds 15–20% [11, 14], more than twice that observed in pT2–3abN0M0 cases from the TAUTEM study treated with neoadjuvant therapy and TEM (LR 7.4%) [22]. Hence, our hypothesis is to treat clinically staged T1N0M0 (cT1N0M0) rectal adenocarcinomas with preoperative CRT to reduce LR below that observed in the TAUTEM trial and increase rectal preservation [22, 23].

Primary objective. To evaluate whether preoperative CRT followed by transanal endoscopic microsurgery (CRT–TEM) increases rectal preservation at 3 years in patients with T1N0M0 rectal cancer without compromising oncologic outcomes, taking into account that local recurrences will be managed with TME, and that, after pathological examination of the specimen, cases presenting surgical or pathological adverse features or with upstaging to ≥ pT2 will also require completion TME according to protocol. Therefore, the challenge is to minimize the number of TMEs, given their well-documented surgical morbidity and functional impairment.

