## Hypothesis and objectives

### Hypothesis

In patients with rectal adenocarcinoma (with biopsy-proven rectal low or moderate grade adenocarcinoma) staged as cT1N0M0 (≤ 4 cm in size and < 10 cm from the anal verge) by endorectal ultrasound (ER) and pelvic magnetic resonance imaging (MRI), preoperative chemoradiotherapy followed by LE(CRT–TEM) is superior to standard LE (TEM) in terms of rectal preservation rate (primary endpoint). Furthermore, CRT–TEM is expected to reduce LR, DR and improve OS, rectal cancer–specific survival, and DFS (at 3 years), without negatively affecting postoperative morbidity or quality of life.

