## Objectives

### Primary objective

To compare the rectal preservation rate between TEM and CRT–TEM at 3 years after surgery.

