## Methods

### Study design

Phase III, multicenter, prospective, controlled, randomized superiority clinical trial evaluating the efficacy and safety of preoperative CRT followed by LE (CRT-TEM group) versus LE alone (TEM group) in clinically staged cT1N0M0 rectal cancer, with rectal preservation as the primary outcome.

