### Sample size

The sample size calculation is based on the primary endpoint, rectal preservation, defined as the absence of the need for completion TME due to discontinuation criteria or local recurrence and rescue to TME. The assumptions are based on data from our group: in T1 tumors, the sm3 rate is 35–40%, with 5–10% of patients presenting adverse pathological factors; in the TAUTEM trial (T2–T3ab), the pCR rate was 44%, therefore a pCR > 55% is expected in T1 cases [22]. Assuming a two-sided test for difference in proportions with α = 0.05 and β = 0.20 (power 80%), 53 patients per group are required to detect as significant a difference between p₁ = 0.60 (TEM) and p₂ = 0.85 (CRT–TEM). Considering a 10% dropout rate, the total sample size will be 106 patients.

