### Statistical analysis

The principal analysis, from which the main study conclusions will be derived, will follow the intention-to-treat (ITT) approach, including all randomized patients. A per-protocol (PP) analysis will also be conducted, including patients from both groups who do not meet withdrawal criteria and who complete the study protocol. Losses to follow-up and their potential impact on outcomes will be analyzed. Pre-specified sensitivity analyses will assess the impact of missing primary endpoint data.

Quantitative variables will be described using mean and standard deviation or, when appropriate (based on the Kolmogorov–Smirnov or Shapiro–Wilk normality tests), median, interquartile range, and range. Categorical variables will be summarized as absolute numbers and percentages.

Comparisons between groups for quantitative variables will be performed using the Student’s t-test (when assumptions of normality and homoscedasticity are met); otherwise, the Mann–Whitney U test will be applied. Categorical variables will be compared using Pearson’s χ^2^ test or Fisher’s exact test, as appropriate.

Survival analyses (local recurrence, distant recurrence, and mortality) will be performed using Kaplan–Meier estimates and compared with the log-rank test.

In addition, an exploratory DFS analysis will be performed stratifying patients according to adverse histopathologic features identified in the local excision (TEM) specimen (e.g., lymphovascular invasion, poor differentiation, tumor budding, and depth of submucosal invasion), and results will be interpreted as hypothesis-generating due to limited power for subgroup analyses.

Statistical significance will be set at *p* < 0.05. When applicable, results will be presented with their 95% confidence intervals (95% CI).

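### The stated aim includes not compromising oncologic outcomes, but the trial's size and its planned difference tests cannot support that conclusion

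*Protocol article*

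**What the plan says.** The aim appears in two forms.

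- **With a not-worse clause.** The Introduction's primary-objective paragraph asks whether CRT followed by TEM "increases rectal preservation at 3 years in patients with T1N0M0 rectal cancer without compromising oncologic outcomes". The abstract's Conclusion says the trial will assess whether the strategy "increases rectal preservation in cT1N0M0 rectal cancer without compromising oncologic safety, quality of life, or bowel function". The abstract's Purpose attaches a similar clause on oncologic safety and quality of life, and the Discussion one on oncologic safety.
- **Without it.** The formal Primary objective is "To compare the rectal preservation rate between TEM and CRT–TEM at 3 years after surgery". The Secondary objectives list recurrence and survival as outcomes to compare at 3 years, and quality of life as an outcome to assess at 1 year.

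The Study design section describes a "randomized superiority clinical trial evaluating the efficacy and safety of preoperative CRT followed by LE". Under Sample size, "53 patients per group are required to detect as significant a difference between" preservation rates of 0.60 and 0.85; no other endpoint enters the calculation. Under Statistical analysis, "Survival analyses (local recurrence, distant recurrence, and mortality) will be performed using Kaplan–Meier estimates and compared with the log-rank test". Quantitative outcomes get a t-test or Mann–Whitney test and categorical outcomes a χ² or Fisher test. The threshold is p < 0.05, and 95% confidence intervals are to be given where applicable. No margin, excluded loss or other criterion says what would count as not compromised.

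**The concern.** A statement that a treatment does not compromise an outcome is a not-worse claim. It can be supported only by showing that a loss large enough to matter is unlikely, which means reading a confidence interval against some limit. A difference test that fails to reach p < 0.05 does not do this, least of all in a trial sized for a different and much larger effect.

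The Discussion acknowledges that CRT may overtreat some of these patients and cause acute and late toxicity, and the Introduction gives local excision alone as the standard for T1N0M0 tumors without adverse features. A conclusion that oncologic outcomes were not compromised would bear directly on whether CRT is added to that standard, so it should rest on evidence that the trial can produce.

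**Working it through.** **Inputs**
- Sample size section: 0.60 versus 0.85, two-sided α = 0.05, power 80%, 10% dropout, 53 per group, 106 in total.
- Introduction, the group's own cohort after local excision: distant recurrence 13.5% overall and 10.2% without high-risk factors, at a median follow-up of 91 months.
- Assumption: distant recurrence of 10% to 13.5% at 3 years. The documents give no 3-year figure, and these rates come from longer follow-up.
- Assumption: a true excess of 10 points, as an example of substantial harm. The documents name no such limit.

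**1. The plan's own figure**
n = (1.96 + 0.8416)² × (0.60×0.40 + 0.85×0.15) / 0.25² = 7.849 × 0.3675 / 0.0625 = 46.2, so 47 per arm. Then 47 / 0.90 = 52.2, so 53 per arm and 106 in total. The figure reproduces with dropout already included. The evaluable number is therefore about 53 × 0.90 = 47.7, or 48 per arm.

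**2. Precision for distant recurrence, equal true rates**
Half-width = 1.96 × √(2p(1−p)/n).

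| p | n = 53 | n = 48 |
|---|---|---|
| 10% | 11.4 points | 12.0 points |
| 13.5% | 13.0 points | 13.7 points |

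For example, 1.96 × √(0.18/53) = 0.114.

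**3. Power to detect a true 10-point excess**
Power = Φ{[d − 1.96√(2p̄(1−p̄)/n)] / √[(p₁(1−p₁) + p₂(1−p₂))/n]}, with d = 0.10.

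| Rates | n = 53 | n = 48 |
|---|---|---|
| 10% vs 20% | 30% | 28% |
| 13.5% vs 23.5% | 26% | 24% |

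For 10% vs 20% at n = 53: (0.10 − 0.136) / 0.0687 = −0.52, and Φ = 0.30. So with a true excess of 10 points, 70% to 76% of such trials would show no significant difference.

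**4. The same check on the planned log-rank scale**
Power for a true hazard ratio of 2 is Φ(√(D/4) × ln 2 − 1.96), where D is the total number of events. The upper 95% limit when the observed ratio is 1 is exp(1.96 × 2/√D).

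| Overall event rate | D of 106 | Power | Upper limit |
|---|---|---|---|
| 5% (assumed) | 5.3 | 12% | 5.5 |
| 10% | 10.6 | 20% | 3.3 |
| 13.5% | 14.3 | 26% | 2.8 |

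If 3-year rates are lower than the cohort's, absolute intervals narrow (±8.3 points at 5% and n = 53), but log-rank power falls further.

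**5. Could a margin be added at this size?**
For illustration, take a 10-point margin, one-sided 0.025, 80% power and equal true rates: n = 7.849 × 2p(1−p) / 0.10². This gives 144 per arm at 10.2% and 184 at 13.5%, before dropout, against 53 planned.

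**The case against.** Several counter-arguments have weight.

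- **No passage says that a null result will be read as safety.** This is correct. A reader might infer that the plan commits the sponsor to that reading, but the documents give no rule for interpreting non-significant secondary results. What stands is narrower: the clause is part of the stated aim, and nothing planned could support it.
- **The plan is not limited to p-values.** Kaplan–Meier estimates are planned and confidence intervals are foreseen where applicable. The Introduction reports the earlier trial's results as differences with intervals. What remains is that intervals are optional here and have no limit to be read against.
- **The clause is not in the formal objective, and the main hypothesis is improvement.** The Hypothesis section says "CRT–TEM is expected to reduce LR, DR and improve OS, rectal cancer–specific survival, and DFS (at 3 years", with a not-worse clause only for postoperative morbidity and quality of life. Difference tests fit an expected improvement. It would therefore be too strong to call the not-worse claim half of the trial's question. But the document then states its aim in two ways, and only one matches the design.
- **Local recurrence is protected.** Under the primary variable it counts as failure however it is managed, and deaths before 3 years may also count under the rule for undocumented status. This cover is partial: the endpoint also counts completion surgery, so a net gain in preservation does not by itself exclude more recurrence. Distant recurrence, disease-free survival and cancer-specific survival have no such cover as endpoints, nor do quality of life and bowel function.
- **Low power for secondary endpoints is usual, and criteria for them may sit in the analysis plan.** Both are true, and low power alone would be no finding. But an analysis plan cannot supply precision that 106 patients do not give.

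**Conclusion.** The concern holds as a mismatch between the stated aim and what the design can show. The abstract, the Introduction and the Discussion attach a not-worse claim to the trial's question; the formal objective and the sample size do not, and no planned comparison could establish it. For distant recurrence the 95% interval is about ±11 to ±14 points, and power for a true 10-point excess is about 24% to 30%. A non-significant result would be likely even with a substantial excess.

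These figures assume a 3-year distant recurrence of 10% to 13.5%, taken from longer follow-up, and an illustrative 10-point excess. They treat recurrence as a binary outcome; the log-rank check points the same way. No calculation was made for quality of life or bowel function, where the argument rests on the type of test alone. The primary comparison of rectal preservation is not affected. The documents do not support the stronger reading that the sponsor plans to declare safety from a null result.

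**What to change.** 1. In the abstract (Purpose and Conclusion), the primary-objective paragraph of the Introduction, and the Discussion, replace the without-compromising clause so that these places agree with the formal Primary and Secondary objectives. Suggested wording: *and to estimate the between-arm differences in 3-year local recurrence, distant recurrence, disease-free survival and overall survival, and in 12-month quality of life and bowel function.*
2. Under Statistical analysis, make 95% confidence intervals for these differences mandatory.
3. In the same section, add: *A non-significant test on these outcomes will not be taken as evidence of safety.*

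A pre-specified margin is not recommended as the main repair, because step 5 of the working shows that it is largely out of reach at this size. The change needs no more patients and leaves the primary test as it is. Its cost is that the trial gives up a not-worse claim that its size cannot support.

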## Hypothesis and objectives

### Hypothesis

In patients with rectal adenocarcinoma (with biopsy-proven rectal low or moderate grade adenocarcinoma) staged as cT1N0M0 (≤ 4 cm in size and < 10 cm from the anal verge) by endorectal ultrasound (ER) and pelvic magnetic resonance imaging (MRI), preoperative chemoradiotherapy followed by LE(CRT–TEM) is superior to standard LE (TEM) in terms of rectal preservation rate (primary endpoint). Furthermore, CRT–TEM is expected to reduce LR, DR and improve OS, rectal cancer–specific survival, and DFS (at 3 years), without negatively affecting postoperative morbidity or quality of life.

## Objectives

### Primary objective

To compare the rectal preservation rate between TEM and CRT–TEM at 3 years after surgery.

### Secondary objectives

To assess the tolerance and adverse effects (acute and chronic) of preoperative chemoradiotherapy (CRT) in the CRT–TEM group (patient safety). To analyze postoperative morbidity and mortality in both groups (surgical outcomes). To evaluate clinical and pathological responses to CRT. To assess quality of life at 1 year after surgery in both groups. To compare long-term oncologic outcomes between groups (at 3 years): LR, DR, DFS, OS and rectal cancer–specific survival at 3 years.

## Methods

### Study design

Phase III, multicenter, prospective, controlled, randomized superiority clinical trial evaluating the efficacy and safety of preoperative CRT followed by LE (CRT-TEM group) versus LE alone (TEM group) in clinically staged cT1N0M0 rectal cancer, with rectal preservation as the primary outcome.

### Patients – study population

Patients diagnosed with rectal tumor will undergo full colonoscopy with multifocal biopsy, which will describe the tumor size and its distance from the anal verge. Staging will include endorectal ultrasound (ER) [24], pelvic magnetic resonance imaging (MRI), and abdominal and chest computed tomography (CT). Baseline serum tumor markers, carcinoembryonic antigen (CEA) and carbohydrate antigen 19–9 (CA 19–9), will also be determined.

### Inclusion criteria

Indication for local excision by a multidisciplinary committee according to ESMO and NCCN guidelines [1, 2] in patients with pathologically confirmed rectal adenocarcinoma on biopsy (with biopsy-proven rectal low or moderate grade adenocarcinoma), located ≤ 10 cm from the anal verge as measured by rigid rectoscopy at the time of endorectal ultrasound (ER). Age ≥ 18 years (both men and women). Women of childbearing potential must have a negative urine pregnancy test at the screening visit. Preoperative staging by ER and/or MRI must confirm T1N0 disease; in the event of discrepancy, the higher category will be adopted as the preoperative diagnosis. Tumor size must be ≤ 4 cm (maximum diameter on MRI). cN0 is defined as absence of suspicious lymph nodes on ERUS/EUS and pelvic MRI; if nodal involvement is suspected on either modality, the patient is considered cN + (higher category) and is not eligible as cN0. ASA score ≤ III. Absence of distant metastases on abdominopelvic CT and chest X-ray (or chest CT if inconclusive). Written informed consent must be obtained before performing any study-specific procedure.

Endorectal ultrasound (ER) staging will follow established criteria as previously described by Hildebrandt [25]. Preoperative pelvic MRI staging will be performed according to standard high-resolution rectal cancer MRI protocols [26, 27]. Tumor size (maximum diameter in mm) will be recorded as a baseline morphological parameter but will not be used as a sole criterion for response assessment in patients undergoing neoadjuvant therapy.

### Exclusion criteria

Preoperative staging by ER or pelvic MRI showing disease beyond T1 or N0 stage; presence of distant metastases; synchronous colorectal adenocarcinomas; poorly differentiated rectal adenocarcinoma [10]; contraindication and/or intolerance to preoperative chemotherapy or radiotherapy.

Unfavorable histopathologic features such as lymphovascular invasion, perineural invasion, and tumor budding cannot be reliably assessed on baseline endoscopic biopsy specimens; therefore, at screening, only tumor differentiation grade is used for eligibility, whereas adverse features are evaluated on the local excision specimen [28].

Patients not eligible for inclusion in the trial will be treated according to the standard clinical practice of each participating center, by means of transanal endoscopic surgery.

